### Sample size and power

A sample size calculation using G-power 3.1 was conducted for the primary outcome measure, defined as the mean difference in the quality of life between two groups at three time points (baseline, 12 weeks intervention, 26 weeks follow-up). We used historical data on the Kidscreen-27 (a measure of QoL) from our own population to estimate the effect size. To detect a median effect size (Cohen’s f = 0.39) with a two-sided significance level of 5% and power of 80% with equal allocation to two arms would require 66 patients in the trial. To allow for 20% drop-out, 80 children are recruited in total.

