The primary objective of the Movementss study is to quantify the short-term (after 12 weeks) and long-term (after 6 and 12 months) effectiveness on quality of life compared to care as usual (CAU) in children aged 6–12 years with MI. We hypothesize that the lifestyle intervention will be more effective than CAU. The second aim is to examine the short- and long-term effects of the lifestyle intervention compared to CAU on outcome measures related to mental and physical symptoms and lifestyle problems such as emotional and behavioral problems, cognitive outcomes, sleeping, eating patterns, and weight status. It is hypothesized that lifestyle improvement will have a positive effect on these mental and physical symptoms. Additionally, the third aim is to investigate the cost-effectiveness of the lifestyle intervention compared with CAU. We assume that intervening in lifestyle at such a young age will result in less expensive care in the long term. Also, this study aims to identify potential moderators of adherence or responders to the treatment (e.g., SES, ethnicity, comorbidity). Finally, qualitative questions will be addressed in this study by examining the potential facilitators and barriers to the lifestyle intervention.

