#### Randomization

The Movementss study is a two-arm randomized controlled trial; patients fulfilling eligibility criteria and willing to participate will be randomized after baseline assessment (1:1 allocation ratio) in either the lifestyle intervention or CAU group using block randomization, with varying random block sizes of 2, 4 or 6. A priori, an independent statistician will prepare a computer-generated randomization schedule stratified for weight (underweight, normal, overweight), sex (male, female), and age (6–8 years, 9–12 years) to ensure that the number of participants in both treatment arms is closely balanced within each stratum. Castor EDC will be used for the actual randomization process. After obtaining informed consent and baseline measurements, the study coordinator will provide the randomization code. Participants, researchers, and practitioners are aware of treatment allocations.

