#### Primary study parameter(s)

Since the design is a repeated-measures RCT, repeated-measures techniques will be used to analyze the difference between the lifestyle intervention and CAU group for the quality of life. The repeated measures techniques will be based on the intention-to-treat principle, in which participants with at least one valid post-baseline follow-up are included. Analyses will be adjusted for the stratification factors (age group, sex). The study results will be reported in accordance with the Consolidated Standards of Reporting Trials (CONSORT) guidelines [51].

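### Baseline quality of life is listed as a time for comparing the arms and left out of the adjustment set; it should be the reference or a covariate, and the primary contrast should be named

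*Protocol article*

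**What the plan says.** The primary objective, in the Background of the protocol article, is to "quantify the short-term (after 12 weeks) and long-term (after 6 and 12 months) effectiveness on quality of life compared to care as usual". All of those times follow the start of treatment.

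Sample size and power defines the primary outcome as "the mean difference in the quality of life between two groups at three time points (baseline, 12 weeks intervention, 26 weeks follow-up". The calculation there is framed as "To detect a median effect size (Cohen’s f = 0.39"; at 80% power and a 5% two-sided level it arrives at 66 children.

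Under Randomization, children "will be randomized after baseline assessment (1:1 allocation ratio", so the baseline score precedes allocation.

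Under Primary study parameter(s), "repeated-measures techniques will be used to analyze the difference between the lifestyle intervention and CAU group for the quality of life". The stated adjustment is: "Analyses will be adjusted for the stratification factors (age group, sex". The baseline KIDSCREEN-27 score is not in that list, although Table 2 schedules it at T0. The article does not say whether the group main effect or the group-by-time interaction is the primary test.

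**The concern.** Randomisation makes the expected arm difference at baseline zero. Listing baseline as a time of comparison therefore does not match an objective about effects after treatment. Read literally, a mean difference between groups over the three times is a group main effect averaged over T0, T1 and T2. That average mixes one zero with two real differences and carries baseline noise into the estimate. The score that probably predicts later scores best sits among the outcomes and is not used as a covariate.

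In a trial sized at 66 evaluable children, a real benefit could be missed and its size understated. The main effect and the interaction come out of the same repeated-measures run, with different nulls and very different power. Because the trial is open label, the choice between them should be settled in the text.

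**Working it through.** **The plan's own figure.** For two equal groups d = 2f, so f = 0.39 corresponds to d = 0.78. An F test with 2 numerator degrees of freedom and noncentrality N·f² = 66 × 0.39² = 10.04 has power 0.80 (0.796 to 0.797, depending on the denominator degrees of freedom) and needs N = 67. This matches 66 within tolerance. Two degrees of freedom is also what a 2-group by 3-time interaction has. A between-groups repeated-measures test over three times needs only 20 to 52 children for correlations of 0 to 0.9, and a one-way two-group comparison needs 54. Neither gives 66.

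**Inputs for the comparison.**
- N = 66 and two-sided 5%, from Sample size and power.
- Assumed: SD 1, compound symmetry, equal arms, and the same effect d at T1 and T2.
- Correlation r = 0.61 to 0.74, also assumed. This is the test-retest range quoted for the KIDSCREEN-27 domains, used as a proxy because the article gives no correlation over 12 to 26 weeks.
- d = 0.78, taking f = 0.39 as the post-baseline effect, and d = 0.5 as an assumed smaller benefit.

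**Formulas.** The standard error is √(4·variance/N).
- *A. Main effect over T0, T1, T2:* effect (0 + d + d)/3 = 2d/3, variance (1 + 2r)/3, t on 64 df.
- *B. Interaction:* noncentrality (2/3)·d²·N/[4(1 − r)], F on 2 and 128 df.
- *C. Mean of T1 and T2 adjusted for T0:* effect d, variance (1 + r)/2 − r², t on 63 df.

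**Numbers put in, d = 0.78, r = 0.61.**
- A: effect 0.52, variance 0.740, noncentrality 0.52/√(4 × 0.740/66) = 2.46, power 68%.
- B: noncentrality (2/3)(0.6084)(66)/(4 × 0.39) = 17.16, power 96.4%.
- C: variance 0.805 − 0.372 = 0.433, noncentrality 0.78/√(4 × 0.433/66) = 4.82, power 99.7%.

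**Results (power at r = 0.61, then r = 0.74).**

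| Test | d = 0.78 | d = 0.5 |
|---|---|---|
| A. Main effect including T0 | 68%, 63% | 34%, 31% |
| B. Group-by-time, 2 df | 96.4%, 99.7% | 65%, 83% |
| C. Post-baseline, adjusted for T0 | 99.7%, >99.9% | 86%, 94% |

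Against C, reading A loses 52 to 63 points at d = 0.5. Reading B loses 21 to 11 points at d = 0.5 and about 3 or less at d = 0.78.

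**Sensitivity to correlation.** At r = 0.3 the powers of A, B and C are 81%, 79% and 99% at d = 0.78, and 45%, 40% and 76% at d = 0.5.

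**Sensitivity to equal effects.** With d = 0.78 at T1 and 0.20 at T2, B has 92% (r = 0.61) and 99% (r = 0.74), while C has 85% and 93%.

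**Type I error.** Simulation with no effect (8,000 replicates) rejected in 5.1% to 5.4% of runs for A and C.

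**The case against.** The strongest reply is that the article commits only to repeated-measures techniques. An interaction model, or a longitudinal model with equal baseline means, fits that wording and uses baseline as the reference. The stated N of 66 fits a 2-df test and not the between-groups main effect. The list of three times may simply describe the measurements entered in the calculation, and the analysis set requires a valid value after baseline. The exact model may be set out in a fuller document that is not shown. Most of this stands: the diluted main effect is one possible reading, not the established plan. The fit of N to 2 df is suggestive and does not prove which test was intended.

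A reader might also infer that the interaction fails to test benefit after treatment. It does test it: with equal baseline means, parallel profiles imply no arm difference at T1 or T2. Nor does baseline adjustment always win; with unequal effects the interaction can have more power than the adjusted post-baseline mean.

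What the reply does not remove is the text itself. One section names a pre-randomisation value as a time of comparison, and another gives an explicit adjustment list without the baseline score. Those are statements to correct, not detail left for later.

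**Conclusion.** The point holds as one of efficiency and clarity. The primary outcome definition should not count baseline as a time at which the arms are compared, and the adjustment list should include the T0 score.

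The size depends on a test that the article does not fix. If it is the group main effect, the estimate falls to two thirds of a constant benefit and power at the protocol's own effect drops below the planned 80% for correlations of 0.61 to 0.74. If f = 0.39 was meant for the three-time average, the post-baseline effect would have to be 0.78 × 3/2 = 1.17. If it is the interaction, there is no dilution; the loss is small at d = 0.78 in that correlation range and moderate at d = 0.5.

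It would be tempting to say that the plan understates the treatment effect by one third. The document does not support that as a statement of fact, because it never says that a main effect including T0 will be reported. Nothing here inflates type I error. The figures rest on compound symmetry, a borrowed correlation and, except where shown, equal effects at T1 and T2.

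**What to change.** In Sample size and power, describe baseline as the reference and not as a time of comparison. In Primary study parameter(s), state that the response is the post-baseline KIDSCREEN-27 scores with the T0 score as a covariate, or use a longitudinal model that constrains the arm means to be equal at baseline. Name the post-baseline arm contrast, with its time or times, as the primary effect. If the effect is expected to differ between 12 and 26 weeks, choose the contrast with that in mind, because a simple average may not be the most powerful choice. Under Secondary study parameter(s), do the same for repeated outcomes that have a T0 value.

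The cost is wording and one degree of freedom for the covariate. It needs no new data and no additional children.

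### Recruiting 80 children covers a 17.5% loss, not the stated 20%: at 20% drop-out 64 remain, two below the 66 required; and the 'median' label does not suit f = 0.39

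*Protocol article*

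**What the plan says.** The section 'Sample size and power' of the protocol article makes these statements:

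- The calculation concerns the "mean difference in the quality of life between two groups at three time points (baseline, 12 weeks intervention, 26 weeks follow-up").
- The effect size is said to rest on the centre's own past data: "We used historical data on the Kidscreen-27 (a measure of QoL) from our own population to estimate the effect size". No means, SDs or correlations are given.
- The effect is named and labelled: "To detect a median effect size (Cohen’s f = 0.39").
- The error rates are fixed: "with a two-sided significance level of 5% and power of 80"%.
- The requirement is that "power of 80% with equal allocation to two arms would require 66 patients in the trial".
- The recruitment target follows: "To allow for 20% drop-out, 80 children are recruited in total".

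**The concern.** A drop-out allowance should leave the required number after the stated fraction has been lost. Here the target and the allowance do not fit together: 80 less 20% is not 66. The section therefore promises 80% power under a loss that it does not cover. Drop-out is a live issue in this trial, because the Discussion itself warns that the intensive programme may prove too demanding and lead families to leave.

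The second issue is the adjective. If 'median' stands for 'medium', as seems likely, it points to a much smaller effect than 0.39. A reader who relies on the word could believe that the trial is sized for a medium effect, and could take a null result as evidence against one.

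**Working it through.** **Inputs, all from 'Sample size and power':** required N = 66 in total with 1:1 allocation; f = 0.39; two-sided 5%; power 80%; three time points; drop-out 20%; recruited N = 80.

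**1. How 80 arises.** 66 × (1 + 0.20) = 79.2, rounded up to 80. This reproduces the stated target.

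**2. The correct step.** Required N / (1 − drop-out) = 66 / 0.80 = 82.5, so 83, or 84 for equal arms.

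**3. What 80 delivers.**
- Remaining after 20% loss: 80 × 0.80 = 64, two fewer than 66.
- Loss that 80 can bear: (80 − 66) / 80 = 14 / 80 = 17.5%.

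**4. Reproducing 66.** The article does not name the test, so this step is an assumption. Take a group-by-time interaction with 2 groups and 3 time points, noncentrality λ = f²N, and degrees of freedom 2 and 2(N − 2), at 5%. The smallest even N with at least 80% power is then 66, which matches the article.

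**5. Power at f = 0.39 under that assumption (f² = 0.1521).**

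| Children with data | λ = f²N | df | Power |
|---|---|---|---|
| 66 | 10.04 | 2, 128 | 80.7% |
| 64 | 9.73 | 2, 124 | 79.4% |

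The shortfall at 64 is 1.3 points against 66 and 0.6 points against the 80% target.

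**6. Sensitivity to the unnamed test.**
- A 1-df two-group test at 2.5% also returns 66, with power falling from 80.6% to 79.3%, but 2.5% is not the stated level.
- A plain two-group test at 5% needs 54, so it is not the calculation behind 66.
- A 2-df test with N − 3 error df gives 79.7% at 66 and needs 67, so it does not reproduce the figure either.

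The two settings that return 66 agree on about 79% at 64.

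**7. The label.** The benchmarks are the usual convention for Cohen's f (0.25 medium, 0.40 large). They are not printed in the article. The value 0.39 lies 0.01 below large and 0.14 above medium. Under the assumption in step 4, f = 0.25 with 64 children gives λ = 0.0625 × 64 = 4.0 and power of about 41%. Reaching 80% for f = 0.25 would take 156 children with data, or 156 / 0.80 = 195 recruited.

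**The case against.** **The shortfall is trivial.** Three recruited children and about half a percentage point below target will not change the trial. This stands as to size. It does not make the sentence correct, since no reading of a 20% loss from 80 leaves 66.

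**Sixty-four need not be the number analysed.** 'Primary study parameter(s)' keeps every child with at least one valid post-baseline assessment, and 'Statistical analysis' mentions multiple imputation. A child lost after the 12-week visit can still contribute. This also stands: 64 is the analysed number only if every drop-out lacks post-baseline data or if only completers are used. The error is in the planning arithmetic, and a reader should not infer that the trial will necessarily miss 80% power.

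**The label drives nothing.** The value 0.39 is printed beside the adjective, is said to come from historical data, and is what the calculation uses. That is right. The word is a poor description and does not show that the assumed effect or the 66 is wrong. If a literal median of historical effects was meant, the text does not say so.

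**A stronger reading to avoid.** A reader might double f to 0.78 SD and call it 7.8 points on the KIDSCREEN T scale. That conversion belongs to a plain comparison of two group means, which needs 54 children, not 66. It also takes the scale's SD of 10 as the SD of this clinical sample, which the article does not give. Relabelling 0.39 as large would likewise be loose, since it falls just below the usual large value. Nor is the unnamed G*Power test a fault here, because an article commonly leaves that detail to the full protocol.

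**Conclusion.** The drop-out allowance is wrong as written. Eighty recruits cover a loss of 17.5%, and covering 20% would take 83, or 84 for equal arms. This part rests only on the article's own figures.

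The consequence is small: power of about 79% instead of just over 80% if 64 children contribute. That figure assumes the 2 × 3 interaction set-up that reproduces 66, and that those lost contribute nothing.

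The adjective attached to f = 0.39 is a minor wording fault, judged against a convention that the article does not print. It matters for interpretation only: under the same assumption the trial has about 41% power at f = 0.25 with 64 children, so a null result would say little about a medium effect.

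**What to change.** Keep N = 80 and restate the allowance, for example: *80 children allow for 17.5% drop-out; at 20% drop-out 64 remain and power is about 79%, just under 80%.* The 79% should be checked against the test option actually used in the full protocol. Delete the adjective 'median' and state f = 0.39 alone, without a replacement label.

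The cost is two edits in one section. Recruitment, design and analysis do not change; the stated power becomes slightly less favourable.

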### Data collection and management

Confidentiality is maintained throughout the current study. The handling of subjects’ personal data is in accordance with the European General Data Protection Regulation (in Dutch: Algemene Verordening Gegevensbescherming, AVG). To maintain anonymity of all data, participants will only be identifiable by a unique code assigned on the data of their inclusion. The code list will be digitally stored on the secured drive of Karakter, which is password protected, and is only accessible to researchers involved in the project. Non-anonymous data (e.g. informed consent documents), will be digitalized and stored in password-secured folders that provide restricted access. All local databases will be secured with password-protected access systems. The online electronic data capture software CASTOR EDC will be used to collect and store questionnaire data. Data collected during an assessment at the location, such as physical measurements, actigraph data, and outcomes of the WISC-V intelligence test, will also be entered and stored in CASTOR EDC. All paper documents are stored in a locker at Karakter Child and Adolescent Psychiatry. Access to this storage is accessible to only a select few researchers.

Parents will be reminded via e-mail (twice) and then via telephone by the researchers to reduce the chance of missing data. During the intake, researchers will explicitly mention 1-year participation to prevent drop-out at the long-term assessments (after 6 and 12 months). After completing these long-term data, families will also receive a small gift to make it more attractive to complete all four assessments. Parents can declare their travel expenses up to 20 euros. Children will receive a small gift after T0, T1, T2, and T3. Participants may withdraw from the study for any reason at any time.

### Statistical analysis

Data will be analyzed using SPSS V.29.0 for Windows (SPSS Incorporated). Descriptive statistics will be performed for baseline characteristics of the study population. Parametric data will be presented as means with SD, and non-parametric distributed variables as median with interquartile ranges (IQRs). A *p*-value < 0.05 will be considered statistically significant. To evaluate the impact of missing data on the outcome measurements, different approaches will be used, such as Multiple Imputation Strategy.

#### Primary study parameter(s)

Since the design is a repeated-measures RCT, repeated-measures techniques will be used to analyze the difference between the lifestyle intervention and CAU group for the quality of life. The repeated measures techniques will be based on the intention-to-treat principle, in which participants with at least one valid post-baseline follow-up are included. Analyses will be adjusted for the stratification factors (age group, sex). The study results will be reported in accordance with the Consolidated Standards of Reporting Trials (CONSORT) guidelines [51].

#### Secondary study parameter(s)

Concerning secondary outcome measurements, repeated measures techniques based on the intention-to-treat principle will be used to analyze the difference between the lifestyle intervention and the CAU group.

To get more insight into the prior beliefs of parents about short-term and long-term success, the outcomes of the 5-item questionnaire will be analyzed using the independent samples *t*-test to compare the lifestyle intervention group with the CAU group. Patient satisfaction and compliance with the intervention will be measured using the satisfaction measurement scale. The outcomes will be evaluated with a repeated-measures design.

The cost-effectiveness of the lifestyle intervention is measured with the TiC-P questionnaire. To assess this outcome, we will use an independent sample *t*-test to compare the lifestyle intervention with the CAU.

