#### Other study parameters

R. Parenting stylesParenting styles are examined using the Brief Scale of Parental Behavior (25 items) (BSBP: English translation of ‘Verkorte Schaal voor Ouderlijk Gedrag (VSOG)’) [48] at T0 (Baseline). This questionnaire is used to assess potential changes in pedagogical style during the intervention. The Brief Scale of Parental Behavior has a 5-point scale that ranges from 1 (*(almost) never*) to 5 (*(almost) always*) [48]. A low score on two subscales indicate inadequate parenting styles, while a high score on the three remaining subscales indicates inadequate parenting styles [48].S. Parenting functioningTo assess changes in family functioning during treatment, the Family Functioning Questionnaire (28 items) (FFQ: English translation of ‘Vragenlijst Gezinsfunctioneren Ouders (VGFO)’) [49] is used at T0 (Baseline). The FFQ has a 4-point scale ranging from 1 (*not applicable*) to 4 (*completely applicable*), with lower scores suggesting more problems with family functioning [49].T. Prior beliefsTo evaluate parents’ previous beliefs on the short-term and long-term efficacy and challenges of the lifestyle intervention, a 5-point scale questionnaire from 0 (*completely disagree*) to 5 (*completely agree*) is used. Prior beliefs are measured at T0 (baseline).U. Patient satisfactionPatient satisfaction and treatment compliance are measured using the GGZ-Jeugdthermometer [50]. This instrument permits institutions to overlook how clients and parents of clients appreciate the care provided. Parents assess their satisfaction with the information they received about the treatment, the team of psychologists, the amount of shared decision-making, and the results of the treatment. Furthermore, parents value their children's experiences during treatment and of their own. Finally, parents can rate their overall experience on a scale of 0 to 10. Patient satisfaction will be measured at T3 (12 months after baseline).

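### Parents' prior beliefs are measured before allocation, so the planned between-arm t-test on them tests a null hypothesis that randomisation makes true; the response scale is also described inconsistently

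*Protocol article*

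**What the plan says.** All places are in the protocol article.

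- **Planned analysis** (Secondary study parameter(s)). The aim is "To get more insight into the prior beliefs of parents about short-term and long-term success", and for this "the outcomes of the 5-item questionnaire will be analyzed using the independent samples" t-test, lifestyle intervention against care as usual.
- **Timing of the measure** (Other study parameters, item T). "Prior beliefs are measured at T0 (baseline"). Table 2 agrees: T0 is the only time point for this questionnaire.
- **Timing of allocation** (Randomization). Eligible patients "will be randomized after baseline assessment (1:1 allocation ratio"), and "After obtaining informed consent and baseline measurements, the study coordinator will provide the randomization code".
- **Blinding** (Randomization). "Participants, researchers, and practitioners are aware of treatment allocations". The primary outcome, KIDSCREEN-27, is rated by parents.
- **Moderators** (Background, last paragraph). The article says that "this study aims to identify potential moderators of adherence or responders to the treatment (e.g., SES, ethnicity, comorbidity").
- **Response scale** (Other study parameters, item T). The instrument is "a 5-point scale questionnaire from 0" (complete disagreement) to 5 (complete agreement).

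**The concern.** A test between arms asks whether allocation made a difference to the variable. Beliefs recorded before allocation cannot have been changed by it. The planned test therefore has no effect to find, and neither possible result carries information: a significant one is a chance imbalance, and a non-significant one was expected from the design.

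The abstract lists prior beliefs among the secondary outcomes, and the test is specified alongside the genuine secondary outcomes at the same p < 0.05 threshold. A chance difference would therefore appear among the trial's results as if it were a finding. The method also does not match the purpose given in the same sentence. Describing what parents believe calls for a description of the answers, not a comparison of arms.

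The scale description adds a smaller problem. If the number of response categories is unclear, so is the score to be summarised.

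**Working it through.** The plan gives no figure for this analysis, so there is none to reproduce. The check is one of timing, followed by the size of the chance rate.

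**Step 1. Order of events.** Consent, then T0 including the prior-beliefs form, then release of the code, then treatment. The belief score is fixed before arm is known. Under 1:1 randomisation its expected value is the same in both arms, so the null hypothesis of equal means is true.

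**Step 2. Rejection rate for one score.** By definition this is α = 0.05. As a check, a simulated six-category variable (0 to 5) fixed before a 40 v 40 split was tested in 10,000 runs. It gave p < 0.05 in 4.95% of runs, the nominal level.

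**Step 3. Rejection rate if each of the five items is tested.** For independent items:

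1 − (1 − 0.05)^5 = 1 − 0.95^5 = 1 − 0.7738 = 0.226.

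Items on one questionnaire are usually correlated. The article gives no correlation, so these values are assumptions (simulation, 40 v 40, 10,000 runs each):

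| Analysis | Assumed inter-item correlation | Chance of at least one p < 0.05 |
|---|---|---|
| One total score | not applicable | 5% |
| Five items | 0.7 | 15% |
| Five items | 0.5 | 18% |
| Five items | 0.3 | 21% |
| Five items | 0 | 23% |

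**Step 4. What the optional moderator analysis could show.** Assume a standardised belief score, one outcome time, residual SD 1 and equal arms. The slope in each arm has variance 1/(N/2) = 2/N, so the difference in slopes has variance 4/N and SE = 2/√N. The difference detectable with 80% power at two-sided 5% is (1.960 + 0.842) × 2/√N:

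- N = 80 (recruited): 2.802 × 0.2236 = 0.63 outcome SD per belief SD.
- N = 66 (required by the sample size calculation): 2.802 × 0.2462 = 0.69.

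Power for a slope difference of 0.3 is about 27% (N = 80) or 23% (N = 66); for 0.5 it is about 61% or 53%. Such an analysis would be imprecise.

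**Step 5. Scale.** The integers 0, 1, 2, 3, 4, 5 are six response points, not five.

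**The case against.** Several points can fairly be made in defence of the plan.

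- **The measure is minor.** Table 2 places prior beliefs under other study parameters, and nothing in the primary analysis depends on this test. This stands, and it limits the importance of the point.
- **The arm means and SDs that come with a t-test would partly describe parents' beliefs.** This also stands. It is the significance test that is idle, not the summary by arm.
- **A difference need not be pure chance.** It could also signal subverted allocation, selective non-completion of the form, or T0 forms filled in after the allocation was known. True, but the article does not plan the test as such a check, which is why the conclusion is conditional on sound randomisation.

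Three stronger readings are tempting and are not supported.

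- A reader might take 18% to 23% as the false-positive risk. That requires five item-level tests, and the article does not say whether items or one score will be analysed. With one score the figure is 5%.
- A reader might infer that the trial overlooks prior belief as an expectancy moderator, given open allocation and parent-rated quality of life. The moderators in the Background are introduced as examples only, and the article condenses a fuller plan that is not shown. The absence of prior beliefs from that list is not a fault that can be established here.
- A reader might say the test is offered as evidence about treatment success. The stated aim is narrower: insight into parents' beliefs about success.

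**Conclusion.** The point holds for the analysis as written. A between-arm significance test is fixed for a variable measured before allocation. Provided that randomisation is sound and the T0 forms are completed before the code is released, the null hypothesis is true by design and the test cannot serve its stated purpose. The chance of a spurious significant difference is 5% for a single total score and up to about 23% for at least one of five separately tested items; the upper end assumes independent items. The scale description contradicts itself. The consequence is modest: no conclusion about effectiveness changes, but an uninformative p-value would be reported with the secondary results.

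**What to change.** 1. **Remove the between-arm t-test on prior beliefs.** Report the answers descriptively, overall and by arm, with the baseline characteristics, for which descriptive statistics are already planned. This costs nothing and needs no new data.
2. **Reconcile the scale description with the form in use**, and state whether items or a total score will be summarised. This is a wording correction.
3. **Optional.** Since the article already aims to identify moderators, prespecify one exploratory interaction of prior-belief score with arm in the KIDSCREEN model, reported as an estimate with a confidence interval and not judged by its p-value. This adds a main effect and an interaction term, and more if the interaction may differ between follow-up times. It will be imprecise with 66 to 80 children, and it cannot separate biased parental rating from genuinely greater engagement with the programme. It should be labelled accordingly.
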